## Abstract

**Background:**

The objectives are to compare the effectiveness of cell phone-supported SMS messaging to standard care on adherence, quality of life, retention, and mortality in a population receiving antiretroviral therapy (ART) in Nairobi, Kenya.

**Methods and Design:**

A multi-site randomized controlled open-label trial. A central randomization centre provided opaque envelopes to allocate treatments. Patients initiating ART at three comprehensive care clinics in Kenya will be randomized to receive either a structured weekly SMS ('short message system' or text message) slogan (the intervention) or current standard of care support mechanisms alone (the control). Our hypothesis is that using a structured mobile phone protocol to keep in touch with patients will improve adherence to ART and other patient outcomes. Participants are evaluated at baseline, and then at six and twelve months after initiating ART. The care providers keep a weekly study log of all phone based communications with study participants.

Primary outcomes are self-reported adherence to ART and suppression of HIV viral load at twelve months scheduled follow-up. Secondary outcomes are improvements in health, quality of life, social and economic factors, and retention on ART. Primary analysis is by 'intention-to-treat'. Sensitivity analysis will be used to assess per-protocol effects. Analysis of covariates will be undertaken to determine factors that contribute or deter from expected and determined outcomes.

**Discussion:**

This study protocol tests whether a novel structured mobile phone intervention can positively contribute to ART management in a resource-limited setting.

**Trial Registration:**

Trial Registration Number: NCT00830622

## Background

The most important factor for sustainable treatment of HIV/AIDS for individuals and programs globally is highly consistent use of highly active antiretroviral therapy (ART). For patients, this means adhering to daily or twice daily medication schedules, typically at a minimum of at least 95% of the time, and for programs this means supporting and monitoring patients to achieve those goals.[1] The World Health Organization and UNAIDS have outlined ambitious goals of universal access to those in need among the 28 million people infected with HIV globally, and include a directive to embrace new technologies to help achieve that goal.[2]

Mobile telephones have transformed telephone communications dramatically in resource limited settings. In Kenya, mobile phones penetration has reached over 60% and Africa has the highest rate of new uptake in the world[3]. The reach of cellular networks among HIV infected persons may be even higher than the general African population since both HIV and wireless network coverage are preferenced to areas of higher population densities such as urban areas and transport routes. Currently, mobile phones are used intensely in personal lives and business transactions in the region. We therefore feel that structured mobile phones communications can substantially improve clinical management of HIV patients in resource-limited settings[4].

No previous RCTs of cell-phones for ART adherence have been reported, thus, no systematic review is available. This protocol outlines our proposed methods of a multi-site randomized clinical trial (RCT) that tests if a novel mobile phone communication intervention improves adherence to HAART, and improves other patient outcomes in Kenya. Patient outcomes assessed include mortality, morbidity, quality of life, social and economic indicators. We hypothesize that the cell phone intervention may directly or indirectly improve these outcomes. If the intervention improves HAART adherence (primary outcome) and the drug effect (suppression of plasma viral load), then health, quality of life, social and economic indicators could all be consequently improved. Since the intervention also provides an enhanced communication link between patients and healthcare providers, patient support may also influence patient outcomes directly, independent of drug adherence. By using intention to treat (ITT) analysis, we will broadly assess the effect of the intervention on patient outcomes. By using sensitivity and subgroup analyses, we will assess the intervention effect more specifically.

## Methods and Design

We registered our clinical trial with ClinicalTrials.gov and received the number NCT00830622.

### Study design

The study is a multi-site RCT. Patients will be randomized to the cell phone (SMS) intervention group versus the standard of care (SOC) control (no SMS) at a 1:1 allocation ratio (see Figure 1 Consort diagram).

**Figure 1 F1:**
[figure not shown]
**Consort diagram of study design**.

### Randomization

A project statistician generated 1:1 randomization numbers for study arm assignments using a random number generating program. The randomization was stratified in a 2:2:1 ratio to the three clinics (the rural clinic having the lower number of assignments). Written allocation of assignment is sealed in individual opaque envelopes marked with study identification numbers which are distributed to all three study clinics in sufficient quantity to allocate the target numbers of participants. After consenting to participate and meeting inclusion criteria, screened subjects are enrolled and immediately afterward are assigned to the randomized study arm by a clinician opening the sealed envelopes to determine allocation. Age, gender, and CD4 T cell counts will be assessed for balance of study arm allocation at each site.

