### Sample size

The primary objectives of this trial to improve adherence to HAART and suppression of HIV viral load evaluated at 12 months. The sample size calculation is based on the comparison between proportions of patients with adherence rates (measured as percent of adherence >95%) in the two groups at 12 months because this is the variable that required the larger sample size. The criterion for significance (alpha) has been set at 0.05. The test is 2-tailed, which means that an effect in either direction will be interpreted.

The sample was calculated using (Cary, NC). With the proposed sample size of 247 and 247 for the two groups (ie assuming a 1:1 allocation ratio), the study will have power of 80% to yield a statistically significant result using a chi-squared test (assuming an intention-to-treat principle for the analysis) at alpha = 0.05/2 (ie using the Bonferroni correction factor for the two primary outcomes).

This computation assumes 10% improvement in 'perfect adherence' over a baseline of 75% determined from rates in a large adherence trial by AMPATH in Western Kenya which we felt is the most representative data available. [7] This difference of 10% was selected as the smallest difference that would be important to detect, in the sense that any smaller difference would not be of clinical or substantive importance. It is also assumed that this difference is reasonable, in the sense that an effect of this magnitude could be anticipated in this field of research.

Assuming attrition rates of approximately 10% we intend to over-enrol by 10% resulting in an enrolment target of at least 534 participants for randomization (267 in the Intervention, and 267 in the Control).

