#### Sensitivity Analyses

Sensitivity analysis and per-protocol analysis includes study subjects who meet certain criteria. For sensitivity, additional analysis of outcomes as stated above will include only subjects who completed follow-up at the primary 12 month endpoint. Because the SMS intervention protocol requires active participation of study subjects to respond and thus conduct the intervention as fully intended, per-protocol analyses will also be performed. Study participants in the intervention arm who respond to the weekly SMS's with an SMS back (active response) at least 80% of the time with the 48 hour time frame will be considered highly protocol-adherent; those who respond 50% to 80% of the time will be considered moderately protocol-adherent; those who respond less than 50% will be considered poorly protocol-adherent; and those that respond less than 20% will be considered least protocol-adherent. Subjects who are randomized to the SMS intervention but never respond with a return SMS, for whatever reason, will be considered as never responding and not included in the sensitivity analysis. We will also perform a sensitivity analysis to assess the impact of potential clustering of patients cared for by the same clinic.

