#### Statistical methods

The intervention arm (SMS) will be compared against the control (SOC) for all primary analysis. We will use chi-squared test for binary outcomes, and T-test for continuous outcomes. For subgroup analyses, we will use regression methods with appropriate interaction terms (respective subgroup × treatment group). Multivariable analyses will be based on logistic regression (See Table 2) for binary outcomes and linear regression for continuous outcomes. We will examine the residual to assess model assumptions and goodness-of-fit. For timed endpoints such as mortality we will use the Kaplan-Meier survival analysis followed by multivariable Cox proportional hazards model for adjusting for baseline variables. We will calculate Relative Risk (RR) and RR Reductions (RRR) with corresponding 95% confidence intervals to compare dichotomous variables, and difference in means will be used for additional analysis of continuous variables. P-values will be reported to four decimal places with p-values less than 0.001 reported as p < 0.001. Up-to-date versions of SAS (Cary, NC) and SPSS (Chicago, IL) will be used to conduct analyses. For all tests, we will use 2-sided p-values with alpha = < 0.05 level of significance. We will use the Bonferroni method to appropriately adjust the overall level of significance for multiple primary outcomes, and secondary outcomes.

To assess the impact of potential clustering for patients cared by the same clinic, we will use generalized estimating equations [GEE] (ref) assuming an exchangeable correlation structure. Table 3 provides a summary of methods of analysis for each variable. Professional academic statisticians ([name]) blinded to study groups will conduct all analyses.

**Table 3 T3:** Variables, Measures and Methods of Analysis

**Variable/Outcome**	**Hypothesis**	**Outcome Measure**	**Methods of Analysis**
1) **Primary**	Intervention improved outcome from baseline to 6 months		
			
a) Adherence at 12 months		Percent adherence in previous 30 days >95% [binary]	Chi-squared test
			
b) Suppression of HIV viral load at 12 months		Viral load ≤400 copies/ml [binary]	Chi-squared test

2) **Secondary** Adherence percentage at 12 months	improvement occurred	Adherence % (>95%) [binary]	Chi-squared test

HIV viral load at 12 months	improvement occurred	Viral load (copies)	T-test

Immune reconstitution (change in CD4 T cell count from baseline)	improvement occurred	Cd4 T-cells/mm^3 ^(continuous)	T-test

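### Randomisation is stratified by clinic but the primary chi-squared tests ignore clinic: valid, but possibly a small, avoidable loss of power

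*Protocol article*

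**What the plan says.** Under Randomization, "A project statistician generated 1:1 randomization numbers for study arm assignments using a random number generating program", and "The randomization was stratified in a 2:2:1 ratio to the three clinics". The 2:2:1 figure is each clinic's share of the assignments, not an arm ratio. The section mentions neither blocks nor any other device that forces 1:1 balance within a clinic.

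Under Statistical methods: "We will use chi-squared test for binary outcomes, and T-test for continuous outcomes". Table 3 names the chi-squared test for both primary outcomes, and the Sample size section plans the trial on that test at "alpha = 0.05/2 (ie using the Bonferroni correction factor for the two primary outcomes".

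Clinic appears in the outcome analyses in two other places:
- Sensitivity Analyses: "We will also perform a sensitivity analysis to assess the impact of potential clustering of patients cared for by the same clinic". The method, under Statistical methods, is "we will use generalized estimating equations [GEE] (ref) assuming an exchangeable correlation structure".
- Table 2 lists clinic, and urban versus rural, as subgroups, to be examined by interaction terms in regression.

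The potential covariates in Table 2 include distance from the clinic and cost of attending it, but not clinic itself.

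**The concern.** A factor used to stratify allocation is normally carried into the main comparison. The three clinics serve quite different populations (lower-income urban, middle-income urban, rural pastoralist), so adherence and suppression could plausibly differ between them. If they do, a test that pools the clinics uses a null variance containing between-clinic variation that a stratified test removes.

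What is at stake is efficiency: somewhat less power and somewhat wider intervals than the same patients could give. The GEE analysis does not repair this. It is a sensitivity analysis, it treats clinic as a cluster although patients are randomised individually within clinic, and robust standard errors from three clusters are unreliable. The subgroup analysis asks whether the effect differs by clinic and leaves the primary test as it is.

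**Working it through.** **The plan's own figure.** The inputs, from Sample size, are 75% versus 85% (10% read as percentage points), two-sided, 80% power, alpha 0.05/2, and 247 per arm. With n = (z_alpha + z_beta)² × (0.75×0.25 + 0.85×0.15) / 0.10²:
- alpha 0.025: (2.241 + 0.842)² × 0.315 / 0.01 = 299.4 per arm
- alpha 0.05: (1.960 + 0.842)² × 0.315 / 0.01 = 247.2 per arm

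The stated 247 therefore matches alpha 0.05 without the Bonferroni split. At 0.025, power (pooled-variance formula) is 70.6% with 247 per arm and 74.3% with 267. That is a separate matter, but it means that 74.3%, not 80%, is the baseline for what follows.

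**Inputs for the comparison.** Clinic weights are 0.4/0.4/0.2 (from 2:2:1). There are 267 per arm, because the primary analysis counts everyone randomised, with missing outcomes as failures. Two-sided alpha is 0.025 (z = 2.241). Assumed, because the article does not give them: clinic-specific control rates, a constant +10 points in every clinic, and rates that already reflect the missing-as-failure rule.

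**Formulas.** Let m_k be the mean of the two arms' rates in clinic k, w_k the clinic weight, and m the overall mean.
- Unstratified null SE: √[2 m(1−m)/n]
- Stratified null SE: √[2 Σ w_k m_k(1−m_k)/n]
- Actual SE of the difference, balance within clinic: √[Σ w_k (pC_k(1−pC_k) + pT_k(1−pT_k))/n]
- Power: Φ[(0.10 − 2.241 × null SE) / actual SE]

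**Worked case, control rates 85/75/55%** (weighted mean 75%).
- The m_k are 0.90, 0.80, 0.60. Σ w_k m_k(1−m_k) = 0.4×0.09 + 0.4×0.16 + 0.2×0.24 = 0.148, against 0.80×0.20 = 0.160 unstratified.
- Null SEs: √(0.320/267) = 0.0346 unstratified and √(0.296/267) = 0.0333 stratified. The ratio is 1.04.
- Actual SE: √[(0.1755 + 0.1155)/267] = 0.0330.
- Power: Φ(0.679) = 75.1% unstratified and Φ(0.768) = 77.9% stratified.

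**Range (same formulas).**

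| Control rates by clinic | Unstratified | Stratified | Gain (points) |
|---|---|---|---|
| 75/75/75% | 74.3% | 74.3% | 0 |
| 80/75/60% (mean 74%) | 72.9% | 74.1% | 1.2 |
| 79/79/59% | 74.7% | 76.2% | 1.5 |
| 85/75/55% | 75.1% | 77.9% | 2.8 |

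**Test size.** Under the null at 85/75/55% with balance forced within clinic, within-clinic variance is 0.1755 against 0.75×0.25 = 0.1875 in total, a ratio of 0.936. The actual size is 2Φ(−2.241/√0.936) = 0.0205, and simulation with 214/214/106 patients gives 0.0206. With simple randomisation within clinic, simulation gives about 0.025, which is nominal. The power gain remains under simple randomisation, at about 3.5 points for these rates.

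**The case against.** The strongest reply is that nothing here is invalid. The chi-squared test does not materially exceed its nominal size under either allocation scheme, it is the test the trial was sized on, and the article does not contradict itself. The article gives no clinic rates, so the loss could be zero. Clinic is also examined elsewhere, in the GEE and subgroup analyses. All of this stands. It limits the point to one of efficiency, but it is no reason to leave the stratification factor out of the primary test.

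A reader might go further than the documents allow in four ways:
- That the standard error is definitely too large and power definitely lost. This holds only if outcome rates differ between clinics.
- That the true type I error is below nominal. This needs enforced 1:1 balance within clinic, which the Randomization section does not describe.
- That the Discussion's remark about heterogeneous populations diluting power supports the point. It concerns a weaker treatment response, which a stratified test does not cure.
- That gains of 6 points or so are in play. Control rates of 90/75/45% would give about that, but with +10 points they require 100% adherence in one clinic's intervention arm, although missing outcomes count as non-adherent.

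**Conclusion.** The point holds as a minor recommendation on efficiency. The primary tests disregard the factor by which allocation was stratified, and neither the GEE analysis nor the subgroup listing changes that. The likely cost is between nothing and about 3 points of power for adherence, depending on how far the clinics differ, under the assumptions of a constant 10-point effect, 267 per arm and alpha 0.025. The same reasoning applies to viral suppression, but the article gives no rates from which to size it. The larger gap between the stated 80% power and the roughly 74% available at alpha 0.025 comes from the sample size calculation and should not be attributed to this choice of test.

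**What to change.** Make the primary test for each binary primary outcome a Cochran-Mantel-Haenszel test stratified by clinic, and report the Mantel-Haenszel relative risk with its confidence interval. Include clinic as a fixed factor in the logistic, linear and Cox models, and keep the plain chi-squared test as a supportive analysis. State under Randomization whether 1:1 balance was enforced within each clinic.

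The cost is a line or two of wording, settled before the data are compared by arm. Clinic is already recorded, and no extra patients are needed. With three strata, the smallest holding about 53 patients per arm (0.2 × 267), sparse data are not a concern, and essentially nothing is lost if the clinics turn out to be alike.

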#### Primary outcomes

The first primary outcome is patient adherence to HAART at twelve months. (See Appendix) This is assessed by self-report using a standard questionnaire of the number of pills missed in the last 30 days and calculating percent adherence based on the expected number of doses taken. Percent adherence will be analyzed as a continuous variable and dichotomous variable. Subjects are considered either 'adherent' or 'non-adherent' using an optimal adherence cut off of > 95% of medications taken as directed.[1] Adherence is assessed at each follow-up visit and 'ever-non-adherent' will be our dichotomous outcome. The twelve month scheduled follow-up (defined, allowing for non-exact timing of clinic attendance, as follow-up up to 15 months if patients not present at 12 months) is the primary analysis. The six month assessment will allow for evaluating trends but is not the primary outcome.

The second primary outcome is suppression of plasma HIV RNA load at twelve months after initiating ART. If patients are adherent to HAART regimens, absorb the drugs normally, and if their virus is not resistant to the HAART drugs in the regimen, then plasma HIV load should be suppressed to below detectable levels (≤400 copies per ml) by six months and remain suppressed thereafter. Due to variability in when patients show up for scheduled appointments, we accept follow-up on or after 20 weeks as the six month outcome visit. Analysis of 'suppressed' (≤400 copies/ml) versus 'failure' to suppress (>400 copies/ml) at twelve months as a dichotomous variable is the primary analysis. However, decrease in plasma HIV load copies from baseline to twelve month follow-up will also be analyzed as the difference in a continuous variable from baseline to twelve months.

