#### Secondary outcomes

The potential benefits of the intervention are quite broad, so multiple secondary outcomes are of interest and were selected through academic collaboration. The secondary outcomes fall under the categories of health, quality of life, social factors, and economic indicators (see Table 1). The primary purpose of taking antiretroviral medications for HIV infection is to maintain or restore health in someone who is HIV infected. Several other factors that contribute to a subject's prosperity or overall well-being may be affected directly (by way of enhanced support mechanisms associated with the intervention), or indirectly (through improvements in health related to HAART effect). We therefore feel it is important to assess each of these outcomes independently.

**Table 1 T1:** Secondary Outcome Measures

**Secondary outcome measures (6 months and 12 months post initiation of HAART)**	**Type**
*Health outcomes*	
Self-reported adherence as a percentage	Binary
Suppressed HIV viral load (in copies)	Continuous
Immune reconstitution (change in CD4 T cell count from baseline)	
Time to virological failure	Continuous
Weight gain [lbs] and BMI	Time-to-event
Occurrence of opportunistic infections (OIs)	Continuous
Time to reporting of adverse drug events (ADEs)	Binary
Deaths (all cause)	Time-to-event
*Quality of life (QOL)*	Time-to-event
SF-12	
Satisfaction with care provided	Continuous
*Social factors*	Continuous
Level of disclosure of HIV status	
Impression of stigma	Binary
Family dyamics	Continuous
*Economic factors*	Continuous
Employment attendance	
Household member school attendance	Continuous
Cell phones lost/stolen	Continuous

HAART = highly active antiretroviral therapy, SF-12 = short form 12 adapted for regional application in Kiswahili.

In addition, we hypothesize that the intervention will lead to improved retention on ART.[5] Because participants are actively traced for twelve month follow-up visits, we will use composite retention outcomes. We define 'retained' as someone who followed-up on their scheduled visit without being traced and is still taking ART versus 'unretained' which includes subjects who stopped taking ART before their twelve month visit, who are lost to follow-up, or required active tracing after missing their scheduled twelve month appointment. We will report each element of the composite endpoints.[6]

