### Data collection

Data collection tools include a baseline questionnaire, follow-up questionnaire (used at 6 and 12 month visits), the SF-12 quality of life assessment adapted for local content, GPS co-ordinates of the clinics and participants homes, and a household roster of economic indicators. Questionnaires include continuous and categorical variables and Likert scales. All questionnaires were designed in English and translated to Kiswahili then back translated to verify meaning. Questionnaires are administered by clinic staff fluent in the languages of participants. In instances where study participants speak only local languages, the clinician translates questions directly. Antiretroviral adherence is assessed at each follow-up visit by inquiring about missed doses in the previous 30 days and calculating percent adherence according to pill counts. A visual analogue scale is used to confirm calculated adherence rates. A weekly study log is kept to record the weekly SMS messages and responses including details related to phone access, medication adherence and health or illness issues as they arose. Telephone communications with subjects in the control arm are also recorded in a similar study log, even though they are not sent the weekly SMS messages. Clinic charts are reviewed for WHO stages and clinical data on health parameters and events. A study register is kept to record follow-up.

Attempts are made to obtain lab data from samples obtained at usual clinical care time points and thus are either collected at the same visit as the study questionnaires are administered or within two weeks if not the same day. The CD4 T cell counts are run on a FACScan (Becton Dickson) at a centralized site. Plasmas for HIV viral load testing (Roche Amplicor) are separated at the central laboratory for the Nairobi clinics, but separated and frozen at -20C and batched for transport from the rural district clinic. All plasmas are frozen at -80C at the central lab. Viral loads are run in batches using manufacturer controls.

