#### Sub-group analyses

Because a large clinical trial on this type of intervention has never been done before, we are interested in the interventions effect on various subgroups and the effect of multiple covariates on treatment outcomes. Subgroups of particular interests and potential covariates proposed are outlined in Table 2. Treatment arms will be compared with respect to potential covariates using continuous and categorical univariate analyses.

**Table 2 T2:** List of subgroups and potential covariates

**Subgroups of interest**	**Potential covariates**
Urban vs. rural	Age
By clinic	Gender
Female vs. male	Distance from clinic
Phone ownership (owned vs. shared)	Income level
Occupational designation	Cost to attend clinic
Level of education	Level of literacy
Usual mode of transportation used	Baseline quality of life
	HIV staging
	Level of disclosure of status
	Crossover into intervention

HAART = highly active antiretroviral therapy.

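### The covariate list cited for the multivariable models (Table 2) omits baseline CD4 count and baseline viral load

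*Protocol article*

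**What the plan says.** Four parts of the protocol article bear on this.

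- **Balance check (Randomization):** "Age, gender, and CD4 T cell counts will be assessed for balance of study arm allocation at each site".
- **Covariate list (Sub-group analyses and Table 2):** "Subgroups of particular interests and potential covariates proposed are outlined in Table 2". The covariate column has ten entries: age, gender, distance to the clinic, income, the cost of attending, literacy, quality of life at baseline, HIV staging, disclosure, and crossover to the intervention.
- **Models (Statistical methods):** "Multivariable analyses will be based on logistic regression (See Table 2) for binary outcomes and linear regression for continuous outcomes". The survival analysis is Kaplan-Meier, "followed by multivariable Cox proportional hazards model for adjusting for baseline variables", and those variables are not named. The main tests are chi-squared tests for binary outcomes and t-tests for continuous ones. Table 3 places adjustment for baseline covariates among the sensitivity analyses, as item 4b.
- **Baseline measurements:** CD4 is a secondary outcome in change form, "Immune reconstitution (change in CD4 T cell count from baseline". For viral load, Primary outcomes states that "decrease in plasma HIV load copies from baseline to twelve month follow-up will also be analyzed". Data collection says of staging: "Clinic charts are reviewed for WHO stages and clinical data on health parameters and events".

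**The concern.** The protocol judges CD4 important enough to be one of only three factors checked for balance, yet it is the only one of the three missing from the list to which the adjusted models are referred. Baseline viral load is missing too, although it is the starting value of the quantity that defines the second primary outcome. Most of Table 2 is sociodemographic or about access to care.

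Two things are at stake, both in the adjusted analyses:

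- If the arms differ by chance in CD4 or viral load, models built from the list as printed would not correct for it. Adding the variable only after seeing the imbalance would be a data-driven choice, which naming covariates in advance is meant to avoid.
- Any precision that these two baseline values could bring is given up.

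**Working it through.** The article gives no figure on this point, so the check is a comparison of its sections.

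**Step 1. Which list do the models use?** The sentence on multivariable analyses points to Table 2 in the clause on logistic regression. The Cox sentence does not point to Table 2, and neither does item 4b of Table 3.

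**Step 2. Compare the balance factors and the baseline laboratory values with the list.**

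| Baseline measure | Named in the balance check | Basis for saying it is measured at baseline | In Table 2 covariates |
|---|---|---|---|
| Age | Yes | Balance check | Yes |
| Gender | Yes | Balance check | Yes |
| CD4 count | Yes | Balance check; change-from-baseline outcome | No |
| Viral load | No | Implied by the decrease-from-baseline analysis | No |
| HIV staging | No | WHO stage from chart review (Data collection) | Yes |

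Two of the three balance factors are in the list. None of the ten covariates is CD4 count or viral load. One of the ten, HIV staging, describes disease severity. It appears to be the charted WHO stage, which is a category and a different measurement from either laboratory value.

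**Step 3. Which analyses are touched?** Viral suppression (a primary outcome) and opportunistic infection (a secondary outcome) are binary, and their adjusted form is the logistic model that cites Table 2. Death is modelled by Cox regression with unnamed baseline variables. The primary chi-squared tests contain no covariates, so editing Table 2 leaves them as they are.

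**Step 4. How large could a chance imbalance be?** With n per arm, the standardised difference between arms in a baseline variable has a 95% chance range of about ±1.96 × √(2/n). With the enrolment target of 267 per arm this is 1.96 × √(2/267) = ±0.17 standard deviations. With the 247 per arm of the sample size calculation it is 1.96 × √(2/247) = ±0.18. The effect of such a difference on an adjusted result depends on how strongly the variable predicts the outcome, and the article does not say. The calculation stops here.

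**The case against.** The case against has several parts.

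- **The list is open.** Its entries are called potential and proposed, and nothing confines the models to them. A reader might infer that a CD4 imbalance would be seen and then left unadjusted. The article does not say so. This lowers the weight of the point, but the only published list still lacks the two variables.
- **The Cox model does not cite Table 2.** A reader might infer that CD4 and viral load are shut out of the mortality analysis. They are baseline variables and fit the wording used, so that inference fails. What remains is that the variables are unnamed.
- **Severity is partly covered.** HIV staging is a partial proxy. This stands, but it replaces neither laboratory value.
- **Prognostic strength is not documented.** The article does not quantify how well CD4 or viral load predicts suppression, infection or death. This also stands. The argument rests on the protocol's own choice of CD4 as a balance factor, and on viral load being the starting value of a primary outcome.
- **Baseline viral load is implied, not stated.** Data collection describes the assay without specifying a baseline sample, but the planned change analysis needs one.
- **Final covariates may be left to an analysis plan that is not shown.** That would excuse a missing list. Here a list is printed and cited, so its content can be reviewed.

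**Conclusion.** The point holds as a minor improvement to secondary analyses. Table 2 omits baseline CD4, the only one of the protocol's three balance factors left out, and baseline viral load, which the protocol's own change analysis implies is measured.

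A reader might go further and infer that the primary results are biased or lose power. The documents do not support that. The primary tests are unadjusted comparisons of randomised arms, and a change to Table 2 does not alter them. A reader might also try to express the loss as power, using the 75% and 85% rates in the Sample size section. Those are planning rates for self-reported adherence, which is not the outcome this change targets. No rates are given there for suppression, opportunistic infection or death, and any share of variance explained by CD4 or viral load would be invented.

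The effect is therefore confined to precision and control of chance imbalance in the adjusted analyses, and its size cannot be stated. The verdict assumes that viral load is measured at baseline and that Table 2 is the working list for the logistic models.

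**What to change.** 1. Add baseline CD4 count, as a continuous variable, and baseline log10 viral load to the covariate column of Table 2. State that both are pre-specified for the adjusted analyses of viral suppression and opportunistic infection and enter whatever the balance check shows.
2. In Statistical methods, name the baseline variables of the Cox model and include baseline CD4 among them. Keep that set small if deaths are few.

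This is a change of wording and needs no new data collection if the baseline samples are taken as implied. The adjusted models carry two more terms. Participants without a baseline value would need the multiple imputation that the Analysis plan already provides for data not directly related to adherence.
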